## Materials and methods

### Study design

A cluster randomized controlled trial will be conducted to examine the effectiveness of participation in the tennis SVG ‘*TopSpin 2K25’* on PL among university students at the Chinese University of Hong Kong (CUHK), beyond their regular tennis PE lessons. In this context, the PE courses refer specifically to the public PE practice courses that are compulsory for non-sports majors, guided by PE teachers, which are credit-bearing. Our study employs cluster randomization at the class level, rather than individual randomization, which is commonly used in educational setting. This approach allows entire classes to be randomly assigned to either the intervention or control group, maintaining the integrity of existing class structures and minimizing disruption to timetables and teaching logistics.

A total of 176 first-year university students enrolled in tennis PE courses will be recruited. These students will be drawn from eight entire classes – four male and four female, with each class comprising 22 students. Although students self-select their PE classes during course registration, random assignment will be conducted at the class level after enrollment is finalized. The classes will be randomly assigned to either the intervention group (two male and two female classes; 88 students) or the control group (two male and two female classes; 88 students).

The intervention group will engage in two 20-min sports video gaming sessions weekly in addition to their regular PE lessons. The intervention will last for six weeks, followed by a three-week follow-up period. Data will be collected at three time points: baseline, post-intervention, and follow-up. The intervention duration of two 20-minute sessions per week was selected based on feasibility within the university schedule and supported by prior research. Röglin et al. [19] conducted a randomized controlled trial in which 15–20-minute exergaming sessions, delivered twice weekly over three months, significantly improved students’ physical self-concept, including strength, coordination, and speed. These findings suggest that even short-duration, structured gaming interventions can elicit measurable changes in physical competence and support physical literacy development.

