### Participants

#### Sample size calculation.

Given that the hypotheses in this study involve both between-subjects comparisons (intervention vs. control groups) and within-subjects measurements across three time points, the sample size was calculated using the *“ANOVA: Repeated measures, within-between interaction”* option in G*Power 3.1 software. Based on an expected medium effect size (f = 0.25), an alpha level of 0.05, and a desired statistical power of 0.80, the required sample size was determined to be 28 participants per group. The choice of f = 0.25 was informed by Cohen’s conventional benchmarks and supported by findings from related educational and exergaming interventions. For instance, Zhao et al. [21] conducted a meta-analysis of 16 randomized controlled trials involving 2,962 students and found that exergames significantly improved PE learning outcomes, with a standardized mean difference (SMD) of 0.45, which corresponds to a medium effect size. Given the educational nature of our intervention and the exploratory context, this estimate was considered both conservative and realistic. To account for an anticipated dropout rate of 20%, the target sample size was increased to 35 participants per group, resulting in a minimum total of 70 participants. To ensure sufficient power and account for unforeseen attrition, more participants than the minimum required will be recruited.

Since this study employs a cluster randomized controlled trial design, it is essential to account for the intra-cluster correlation (ICC) to avoid underestimating the required sample size. Participants within the same class may exhibit correlated outcomes due to shared learning environments and peer interactions. To adjust for clustering, we applied the design effect formula:

Design Effect=1+(m−1)×ICC

Where:

*m* = average cluster size (22 students per class)*ICC* = assumed intra-cluster correlation (conservatively estimated at **0.02** based on similar educational interventions)

Thus:

Design Effect=1+(22−1)×0.02=1+21×0.02=1.42

The adjusted sample size becomes:

70×1.42≈100 participants

To ensure adequate power and account for potential attrition and clustering effects, we plan to recruit 176 participants across 8 classes, which exceeds the adjusted minimum requirement.

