### Randomization

Each semester, CUHK offers seven male and seven female tennis PE classes, all taught by different teachers but following standardized content and assessments. For this study, simple randomization will be used. Four male and four female entire classes will be randomly selected by drawing lots. Among these, two male and two female entire classes will be further randomly assigned to the intervention group using the same method.

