### Data analysis

Descriptive statistics, including means and standard deviations, will be calculated for university students’ video gaming time, gaming frequency, physical activity levels, physical literacy, reaction time, and eye-hand coordination across all relevant subscales and instruments. To examine baseline differences between groups in the cross-sectional study, one-way analyses of variance (ANOVAs) will be conducted.

To evaluate intervention effects, mixed-effects models will be employed instead of simple repeated-measures ANOVAs to account for the hierarchical structure of the data and potential intra-cluster correlation among participants within the same class group. This approach addresses the reality that, although courses follow standardized content, variability in teaching style, instructor enthusiasm, and informal reinforcement of the intervention is inevitable in real-world PE settings. Mixed-effects models will include fixed effects for time (baseline, post-intervention, follow-up) and group (intervention vs. control), as well as random effects for class clusters to capture variability across different teaching contexts. These models will assess both main effects and interaction effects, providing more accurate standard error estimation and valid statistical inference.

For secondary outcomes (motivation, cognitive knowledge, social engagement, and physical activity), similar mixed-effects or generalized estimating equation models will be applied, depending on distributional assumptions. Multiple linear regression analyses will explore predictive relationships between PL and physical activity levels, with SVG gaming included as a potential mediator or moderator. Covariates such as baseline physical activity, prior SVG experience, and demographic characteristics (age, gender) will be adjusted for in all models. Interaction effects between the intervention and participant characteristics (e.g., gender, gaming experience) will also be examined to identify subgroup differences.

To enhance the interpretability and transparency of our findings, partial eta-squared will be reported for all primary outcomes to indicate the magnitude of observed effects. Additionally, 95% confidence intervals will be provided to reflect the precision of the estimates and the range within which the true effect is likely to fall. These metrics will support a more nuanced understanding of the intervention’s impact and facilitate comparison with other studies.

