To ensure the integrity of the analysis, the following procedures will be used to address missing data. Participants with more than 20% missing responses on key outcome measures (e.g., physical literacy or physical activity questionnaires) may be excluded from specific analyses. All decisions regarding missing data handling will be documented in the final report, including the rationale for exclusion or imputation. All statistical analyses will be performed using SPSS Version 30 for Windows, with the significance level set at *p* < 0.05.

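### The plan aims to identify subgroup differences at p < 0.05, but its gender-by-intervention test compares four cells of two single-sex classes and can estimate a gender difference only very imprecisely

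*Protocol article*

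**What the plan says.** The subgroup plan is one sentence in the Data analysis section of the protocol article: "Interaction effects between the intervention and participant characteristics (e.g., gender, gaming experience) will also be examined to identify subgroup differences". The list of modifiers is introduced by way of example. All statistical analyses are run "with the significance level set at *p* < 0.05".

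The structure of the groups is given elsewhere. Study design describes eight classes, "four male and four female, with each class comprising 22 students", with the "intervention group (two male and two female classes; 88 students") and the same composition in the control group. Randomization says the tennis classes are "all taught by different teachers but following standardized content and assessments".

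The main models include "random effects for class clusters to capture variability across different teaching contexts". For the secondary outcomes, similar mixed-effects models or generalized estimating equations (GEE) may be used, depending on distributional assumptions. Data analysis also concedes that "variability in teaching style, instructor enthusiasm, and informal reinforcement of the intervention is inevitable in real-world PE settings".

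Exploratory wording does appear in the article, but it is attached to other things: the regressions of physical activity on physical literacy, the cognitive and social measures, and the context of the sample size calculation. It is not attached to the interaction tests.

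**The concern.** Gender and gaming experience are listed side by side as characteristics of participants, but they are different kinds of variable in this design. Gaming experience varies within a class. Gender does not: every student in a class has the same gender, so all information on whether the intervention effect differs by gender comes from comparing whole classes. Each arm-by-gender cell holds two classes and two teachers. The protocol itself expects teachers to differ, including in how far they informally reinforce the intervention, and with two teachers per cell such differences can look like a gender difference.

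What is at stake is a report that the game works for one gender and not the other, presented as an identified finding although it rests on eight class means. The main comparison between arms is not affected by this point.

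**Working it through.** **Inputs from the protocol article.** Eight classes of 22, two per arm-by-gender cell (Study design). One teacher per class (Randomization). An "assumed intra-cluster correlation (conservatively estimated at 0.02 based on similar educational interventions") (Sample size calculation). Expected effect f = 0.25, which for two groups is d = 2f = 0.5 SD, and a cited standardized mean difference of 0.45 (same section). Significance level 0.05 (Data analysis), taken here as two-sided because the article does not say.

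**The plan's own figure.** The article gives no figure for the subgroup tests. Its clustering adjustment reproduces: design effect 1 + 21 × 0.02 = 1.42, and 70 × 1.42 = 99.4, stated as about 100. The same design effect is used below.

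**Precision of the gender-by-intervention contrast.** In SD units, for one unadjusted measurement:

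- Variance of a class mean: 0.02 + 0.98/22 = 0.0645 (equal to 1.42/22).
- Variance of a cell mean over two classes: 0.0645/2.
- The interaction combines four cell means, so its variance is 4 × 0.0645/2 = 0.129 and SE = 0.359 SD.
- Degrees of freedom: 8 classes − 4 cells = 4, with critical t = 2.776.
- 95% interval half-width: 2.776 × 0.359 = 1.00 SD.
- Power from the noncentral t distribution on 4 df: 16% for an interaction of 0.45 SD and 19% for 0.5 SD. About 1.35 SD is needed for 80% power.
- At assumed intra-cluster correlations of 0.05 and 0.10, power for 0.5 SD falls to 15% and 11%.

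**Type I error if the error term is not at class level.**

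- Class variance omitted from the tested effect: 2 × [1 − Φ(1.96/√1.42)] = 2 × [1 − Φ(1.645)] = 0.10. At assumed correlations of 0.05 and 0.10 it is 0.17 and about 0.26.
- GEE with uncorrected robust errors. In a cell with two class means that differ by D, each residual is ±D/2. The robust variance of the cell mean is (2 × D²/4)/2² = D²/8, while the unbiased estimate is D²/4, so the variance is halved. Comparing with 1.96 then rejects whenever |t| on 4 df exceeds 1.96/√2 = 1.386, which has probability 0.24.

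**Chance of at least one false-positive interaction.** The article does not say which outcomes are covered, so the count is an assumption: four (the named secondary outcomes) to seven (adding reaction time, eye-hand coordination and perceived physical literacy). With the two named modifiers treated as independent and an assumed correlation between outcomes:

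| Outcomes | Correlation 0 | 0.5 | 0.8 |
|---|---|---|---|
| 4 (8 tests) | 0.34 | 0.29 | 0.22 |
| 7 (14 tests) | 0.51 | 0.41 | 0.27 |

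The entries at zero correlation are 1 − 0.95^8 and 1 − 0.95^14. The others come from simulation of equally correlated normal statistics. Further modifiers would raise all of them.

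**The case against.** Several stronger readings are tempting, and the article does not support them.

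- A reader might infer that gender cannot be separated from teacher at all. That would be so with one class per cell. Here each cell has two classes with different teachers, and classes of each gender are randomised between arms, so teacher is nested and replicated within cells. The interaction can be estimated against class variation, and the planned class random effect is directed at this. The accurate word is imprecise.
- A reader might infer that the plan will run the gender test at participant level and so has a 10% false-positive rate. Data analysis plans class random effects, so that rate is conditional. The text does not settle whether those effects cover class differences in change over time, or whether GEE would carry a small-sample correction.
- A reader might infer that every outcome is tested for interaction. The sentence names none and stands in a paragraph that opens with the four secondary outcomes.
- A reader might call a false gender finding likely. Under these assumptions, even the chance of any false-positive interaction is at most about one half, and gender accounts for only part of it.

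It is also fair that a closed subgroup list and a multiplicity rule are often left to an analysis plan that is not shown, so their absence alone is no finding. None of the five hypotheses concerns a subgroup, 95% confidence intervals are promised, and low power for interactions is usual. Baseline adjustment would probably improve the precision computed here. The between-class limit does not apply in the same way to gaming experience.

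What these arguments leave standing is the stated aim. The article does not merely omit a caveat: it says the tests serve to identify differences, and it treats gender as if it varied between students within a class.

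**Conclusion.** The point holds as one of overstated purpose and weak information. If the gender test uses a correct class-level error term, it has about 4 df, an interval of about ±1.0 SD and 16% to 19% power for an interaction as large as the main effect the trial expects. If it does not, its type I error is about 10% at the protocol's own intra-cluster correlation, or about 24% with uncorrected robust GEE errors. Neither case supports an identified gender difference. Across both named modifiers, the chance of at least one false-positive interaction is about 0.22 to 0.51.

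The precision and power figures assume 22 students per class and one unadjusted measurement. The 24% assumes large-sample critical values. The 0.22 to 0.51 range rests on assumed outcome counts and correlations and on independent modifiers. The correction is worth making before analysis, but it does not touch the primary comparison.

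**What to change.** In Data analysis, replace the purpose clause of the interaction sentence with wording such as: Interactions of the intervention with gender and with prior gaming experience are exploratory; they will be reported as estimates with 95% confidence intervals and will support no subgroup conclusion.

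Add for gender: The interval uses class-level degrees of freedom (about 4), with a small-sample correction if GEE is used; with two classes per arm-by-gender cell, a gender difference is only weakly distinguishable from differences between classes and teachers. The text should not say that gender is inseparable from teacher, because it is not.

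The cost is a change of wording and a specified degrees-of-freedom method. No data collection changes. The sponsor gives up a subgroup claim that the design cannot support.

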Each participant in the intervention group will be required to attend two 20-minute gaming sessions per week, in addition to their regular PE classes. The SVG Corner will be open Monday to Friday, from 10:00–13:00 and 14:00–18:00. Due to equipment limitations (2 consoles with a total of 8 controllers), each session has limited quota. If a session reaches its quota due to the first-come-first-served arrangement, we will arrange an alternative time slot to accommodate affected participants. The attendance will be tracked weekly, in case where participants are unable to fulfill the attendance requirement, we will contact them via email to arrange make-up sessions. This ensures that all participants can fulfill the attendance requirement and receive the full intended dosage of the intervention.

To minimize contamination bias, students in the control group will not be provided access to the SVG Corner and will be advised not to engage in tennis-themed sports video gaming independently during the study period. While we cannot fully restrict external gaming behavior, participants will be informed of the importance of maintaining their assigned condition and asked to report any SVG-related activity outside the study. This will help us monitor potential crossover and account for it in the final analysis.

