The first two sessions will include guided tutorials within the game to help participants become familiar with the controller layout and basic tennis concepts. For example, the initial tutorial focuses on repositioning, requiring players to return to the center area behind the baseline after each shot. An instructional video will explain the importance of repositioning and demonstrate how to control the avatar. Participants must successfully complete six repositioning tasks to move forward. From the third session onward, participants will engage in both singles and doubles matches, playing with or against other participants. No gaming sessions will be provided to the control group. Participants may withdraw from the intervention if they experience scheduling conflicts, physical discomfort, musculoskeletal or cardiovascular conditions, or are unable to comply with the intervention protocol. To support adherence, PE teachers and research assistants will regularly remind participants to attend their gaming sessions. Additionally, all participants in the intervention and control groups will receive four participation marks in their PE course upon completing the study.

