### Data collection

This study will employ both self-reported and objective measures to comprehensively assess participants’ PL, engagement in physical activities, and sports video gaming habits.

Self-reported data will be collected through a structured set of online questionnaires (see Appendix 1), which include items on video gaming behavior, physical activity levels, physical literacy, and demographic information. These questionnaires will be administered by trained research assistants using Qualtrics, a secure and institution-approved online survey platform. Access to the survey will be provided via a secure link or QR code, distributed to students by their teachers.

Objective measures will include assessments of simple reaction time and eye-hand coordination, conducted using the Ruler Drop Test (RDT) and the Alternate Hand Wall Toss Test (AHWT), respectively. Additionally, a knowledge-based quiz will be administered to evaluate participants’ cognitive understanding of tennis (see Appendix 2).

All assessments will be conducted during scheduled PE tennis lessons at the CUHK. Data collection will occur at three time points: baseline, post-intervention, and a three-week follow-up. Baseline data collection is scheduled for the first week of the second semester (early January 2026), during the same lesson in which participants are recruited. This will be followed by a six-week sports video gaming (SVG) intervention. Post-intervention assessments will be conducted in Week 8 (early March 2026), and a three-week follow-up assessment will take place in Week 11 (late March 2026).

The participant timeline is illustrated in Fig 1. To ensure consistency across all groups, identical procedures and instruments will be used. All assessments will be administered by the principal researcher in collaboration with trained research assistants. A summary of the measurement tools and outcome variables is provided in Table 1.

**Table 1 pone.0343594.t001:** Summary of measurements in this study.

Instrument/Method used	Outcome assessed	Type	Physical literacy domain	Reference
Custom questionnaire on video gaming	Video gaming habits and demographics	Self-reported	Not applicable	Developed by researcher
International Physical Activity Questionnaire – Short Form (IPAQ-SF)	Physical activity level	Self-reported	Physical	[22]
Perceived Physical Literacy Instrument (PPLI)	Perceived physical literacy	Self-reported	Affective, social, cognitive	[23]

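### The 20% missing-data rule is discretionary, has no stated unit and removes students rather than scores, although the planned mixed model can keep partial records

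*Protocol article*

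**What the plan says.** The last paragraph of Data analysis in the protocol article sets out how missing data will be handled. Its only concrete rule is "Participants with more than 20% missing responses on key outcome measures (e.g., physical literacy or physical activity questionnaires) may be excluded from specific analyses". It then adds "All decisions regarding missing data handling will be documented in the final report, including the rationale for exclusion or imputation". The article does not say whether the percentage refers to items within a questionnaire, to one visit or to all three visits. It gives no criterion for choosing exclusion over imputation.

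Earlier in the same section, intervention effects are to be estimated with mixed-effects models that have time (three assessments) and group as fixed effects, "as well as random effects for class clusters to capture variability across different teaching contexts". No student-level random effect is stated. For motivation, knowledge, social engagement and physical activity, either a mixed model or generalised estimating equations (GEE) may be used.

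Three other places bear on the point:

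- Sample size calculation allows for "an anticipated dropout rate of 20" per cent.
- Intervention lists grounds on which a student may withdraw from the intervention, ending "or are unable to comply with the intervention protocol".
- Intervention also says of gaming outside the study: "This will help us monitor potential crossover and account for it in the final analysis".

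**The concern.** Classes are randomised, so the protected comparison is between all students of the classes allocated to each arm. A rule that drops students because of what they left blank at Week 8 or Week 11 selects on events after allocation. Because it works analysis by analysis, the motivation comparison and the physical activity comparison could rest on different students. Because it is discretionary, the analysed set can be settled after the data are in.

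The rule also sits badly with the chosen model. A mixed model over three assessments does not need complete students: a student with baseline and Week 8 scores contributes both, even without Week 11. Excluding the student discards information that the model was able to use.

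The open promise to account for outside gaming is a second unspecified adjustment on something that happens after allocation. Nothing in the article fixes an analysis that keeps every student in the allocated arm whatever the attendance or crossover.

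**Working it through.** **The plan's own figure.** The only figure tied to missing data is the attrition allowance in Sample size calculation: 28 / (1 − 0.20) = 35 per group, 70 in total; 70 × 1.42 = 99.4, about 100. The inflation reproduces. This 20% is a planning allowance for dropout and is separate from the 20% exclusion threshold.

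**When the rule is triggered.** Scale lengths are from Data collection; there are three assessments. The rule needs strictly more than 20%.

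| Unit counted | Smallest gap that triggers it | Share |
|---|---|---|
| Four APLQ items, one visit | 1 of 4 | 25% |
| Nine PPLI items, one visit | 2 of 9 | 22% |
| 24 SMS-6 items, one visit | 5 of 24 | 20.8% |
| Visits, one measure | 1 of 3 | 33% |

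The same threshold therefore means any single blank on one scale and five blanks on another. If visits are counted, it means any single missed visit.

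**How many students.** 0.20 × 176 = 35.2. About 35 students could lose a valid Week 8 score, but only if the percentage is counted across visits and every dropout misses Week 11 alone. That is a ceiling, not an expectation.

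**Precision if missingness is unrelated to outcome.** At that ceiling, dropping 20% of independent students raises the standard error by a factor of √(1/0.80) = 1.118, about 12%. It rises by less once part of the variance lies between classes. No bias arises.

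**Bias.** In one arm let p be the share excluded, R the mean change from baseline in those retained and E the mean change in those excluded. The full-arm mean is (1 − p)R + pE, so excluding shifts it by R − [(1 − p)R + pE] = p(R − E). The shift in the between-arm contrast is p_I(R_I − E_I) − p_C(R_C − E_C), with I for intervention and C for control. The documents give none of these four quantities per arm, so neither sign nor size follows.

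A constant deficit does not produce bias here. If excluded students score δ lower at every visit, their change is (y8 − δ) − (y0 − δ) = y8 − y0. Then E = R and the shift is zero.

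**An assumed example.** A simulation took 88 per arm, correlation 0.5 between visits, ICC 0.02, and 20% of each arm missing Week 11. Dropout was tied to low Week 8 scores in the intervention arm and random in control. Week 8 was analysed by regression on arm and baseline.

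| True effect (SD) | All Week 8 data | Students without Week 11 excluded |
|---|---|---|
| 0 | 0.00 (SE 0.130) | 0.15 (SE 0.142) |
| 0.45 | 0.45 (SE 0.130) | 0.60 (SE 0.142) |

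The 0.15 SD comes from selective dropout that was built in, under the across-visits reading. Swapping the arms would reverse its sign. It shows that the rule can bias a comparison, not that it will here.

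**The case against.** The strongest defence is that the rule is about items. In Data collection, responses are answers to questionnaire items, so the natural reading is missingness within a questionnaire, and a missed Week 11 would then not clearly cost Week 8. A mixed model copes with a missing visit score but not with blanks inside a scale, so some scoring threshold is needed. Exclusion is permissive and limited to specific analyses, imputation is mentioned, and decisions will be reported. Finer rules commonly sit in an analysis plan.

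Much of this stands. A reader might infer that the rule throws away valid Week 8 data from 35 of 176 students. The text does not support that as a statement of fact, because it needs both conditions given with the ceiling above. The need for a scoring threshold is also accepted.

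A reader might also infer that the effect will be inflated, since only the intervention arm has sessions to fail. The documents do not show this. The withdrawal described is from the intervention, not from assessment. Both arms are tested in scheduled PE lessons with the same procedures, and both earn four participation marks for completing the study.

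What the defence does not answer is that the sentence, as written, excludes participants rather than scores, leaves the unit open and leaves the choice to discretion. Reporting the choice afterwards is disclosure, not a rule fixed in advance. The defect lies in what the article states, not in detail it leaves out.

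**Conclusion.** The point holds in limited form. The stated rule can remove students of randomised classes on data arising after allocation, can give each outcome its own analysed set, and can discard scores that the planned model could use. It is triggered by as little as one blank item of four or, if counted across visits, one missed visit of three.

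The size and direction of any bias are unknown. Bias in the group-by-time contrast requires excluded students to differ in change, not merely in level, and the shifts to differ between arms. If missingness is unrelated to outcome, the cost is precision only, at most about 12% on the Week 8 standard error under the ceiling above.

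The model as described also needs one addition. Validity under missing at random requires the correlation within a student to be modelled, and the article states a random effect for class only. Ordinary GEE is not generally valid under missing at random. The rule should be changed before analysis, but it does not by itself invalidate the trial.

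**What to change.** Replace the exclusion sentence in Data analysis with:

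> All consented students are analysed in the arm their class was allocated to, regardless of sessions attended or outside gaming, using every available measurement in a mixed model with random effects for class and student. The 20% threshold applies only to scoring one scale at one visit: above it that score is set to missing and the student stays in the analysis.

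State how a score is formed when 20% or fewer of its items are missing. Where GEE is used, handle missing visits by multiple imputation or weighting.

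Keep two things as labelled sensitivity analyses only: excluding students with more than 20% missing, with the unit defined, and any adjustment for gaming by control students.

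The cost is a change of analysis wording and some added modelling. No new data, visits or recruitment are needed.
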